### 4.3 EXCLUSION CRITERIA

Subjects will be ineligible for this study if they meet **any one** of the following criteria:

1. Clinically significant cardiovascular, respiratory, renal, gastrointestinal, hematologic, neurologic, thyroid, or any other medical illness or psychiatric disorder, as determined by the Investigator and/or Medical Monitor.
2. Positive test for HAV IgM, HBsAg, or HIV antibody. In Parts 1 and 2, positive HCV serology is exclusionary.
3. Any condition that, in the opinion of the investigator, would compromise the study's objectives or the well-being of the subject or prevent the subject from meeting the study requirements.
4. Participation in an investigational drug trial or having received an investigational vaccine within 30 days or 5 half-lives (whichever is longer) prior to study medication
5. Clinically significant abnormal ECG findings. Particularly, a history or family history of prolonged QT syndrome (e.g., torsade de pointes) or sudden cardiac death; or a corrected QT interval (QTc) > 450 milliseconds for male subjects and > 470 milliseconds for female subjects at the Screening Visit.
6. Clinically significant blood loss or elective blood donation of significant volume (i.e., > 500 mL) within 60 days of first dose of study drug; > 1 unit of plasma within 7 days of first dose of study drug
7. Abnormal heart rate, respiratory rate, temperature or blood pressure values outside of the normal range (evaluated in a semi-recumbent or recumbent position after 5 minutes of rest). One repeat measurement after an additional 5 minutes of rest is permitted.
8. Evidence of active infection (other than CHC infection in subjects enrolled in Part 3).
9. Unwilling to abstain from alcohol for 48 hours prior to the start of dosing through the study completion visit.
10. History of regular alcohol intake > 7 units per week of alcohol for females and > 14 units per week for males (one unit is defined as 10 g alcohol) within 3 months of screening visit.
11. For healthy subjects (Parts 1–2), history of regular use of tobacco (i.e., ≥ 10 cigarettes per day) or nicotine-containing products within 3 months of the screening visit. For subjects with CHC infection, history of regular use of tobacco- or nicotine-containing products is allowed.
12. The subject has a positive pre-study drug screen. A minimum list of drugs that will be screened for includes amphetamines, barbiturates, cocaine, opiates, cannabinoids, and benzodiazepines. Subjects with CHC may be included if they have a positive result for cannabinoids at screening. However, they must be willing to abstain from cannabinoid use throughout the duration of the study.

13. In Parts 1-2, the use of concomitant medications, including prescription, over the counter medications, or herbal medications within 14 days prior to the first dose of study medication is excluded, unless approved by the Sponsor's Medical Monitor. PRN use of a nonsteroidal anti-inflammatory drug (NSAID) is permitted.
14. For subjects in Part 3, the use of prescription and over the counter medications deemed necessary to maintain the health status of the subject are permitted, if approved by the Sponsor's Medical Monitor. PRN NSAID use is permitted. Further guidance for the use of prior medication in subjects with CHC can be found in Section 5.7.
15. Subjects must not have received any drug known to be a strong inducer or inhibitor of CYP450 enzymes within 2 weeks prior to study drug dosing (Appendix C).
16. Exposure to more than four new investigational entities within 12 months prior to the first dosing day.
17. Abnormal biochemistry or hematology laboratory results obtained at screening. Elevated bilirubin in subjects with suspected Gilbert's disease is allowed.

A subject with a clinical abnormality or laboratory parameters outside the reference range for the population being studied may be included if the Investigator determines the finding is unlikely to introduce additional risk factors and will not interfere with data interpretation. A single repeat laboratory evaluation is allowed for eligibility determination. The Investigator is encouraged to discuss any laboratory abnormalities which are considered potentially clinically significant with the Sponsor Medical Monitor prior to randomization.

Additional exclusion criteria for subjects with CHC infection:

18. History of clinical hepatic decompensation, e.g., variceal bleeding, spontaneous bacterial peritonitis, ascites, hepatic encephalopathy or active jaundice (within the last year)
19. For all MAD Cohorts (except subjects with compensated cirrhosis), a liver biopsy within two years or Fibroscan evaluation within 6 months prior to randomization that demonstrates cirrhosis (Knodell score > 3, Metavir score > 3, Ishak score > 4). Fibroscan liver stiffness score > 10.5 kPa.
20. Prior treatment for CHC with direct acting antiviral agents
21. Serum alanine aminotransferase (ALT) concentration > 5 x ULN
22. Evidence on screening liver ultrasound of hepatic mass or lesion concerning for malignancy.

#### 4.4 SUBJECT SCREENING AND ENROLLMENT

Screening procedures will occur when a subject signs and dates an IRB/IEC/EC approved informed consent form (ICF) and provides authorization to use protected health information. The informed consent form will be completed prior to any study-specific procedures. For healthy volunteers screening criteria satisfied under a generic consent

within the screening window required by this study may be allowed at the sponsor's discretion. For subjects with CHC infection, screening procedures that are standard of care and have been undertaken prior to consent do not need to be repeated if they were conducted within the eligible screening period, unless otherwise specified.

To enroll, the investigator will verify eligibility according to all inclusion and exclusion criteria (Sections 4.2 and 4.3). For Parts 1, 2 and 3, eligible subjects will be assigned the next available subject number from a randomization list provided by the study statistician. Only the study pharmacist will have access to the corresponding treatment assignment. Any questions regarding eligibility should be addressed to the Sponsor's Medical Monitor prior to randomization.

#### **4.5 SUBJECT DISCONTINUATION**

Subjects are free to discontinue their participation at any time during this clinical trial. The investigator has the right to remove any subject from treatment with study drug or participation in the study. However, Alios requests that the investigator consult with the Sponsor's Medical Monitor before prematurely removing a subject. For subjects that discontinue study drug prematurely, sites are encouraged to follow these subjects as prescribed in this protocol as much as possible as this is the primary mechanism to ensure subject safety.

Any subject who decides to discontinue participation in the study, or meets the discontinuation criteria specified below, should undergo early discontinuation procedures (Section 4.5.2). Subjects that discontinue for safety reasons will not be replaced.

##### **4.5.1 Subject Discontinuation Criteria**

The primary consideration in any determination to discontinue a subject's participation must be the health and welfare of the subject. Reasons for discontinuation may include, but are not limited, to the following:

- An adverse or serious adverse event (AE/SAE), drug reaction, or complication, whether related or not to study drug, which precludes continuation of treatment with study drug. This includes the development of allergic reactions or other potentially serious drug reactions to the study medication.
- Noncompliance with study drug dosing.
- Noncompliance with study procedures.
- Lost to follow-up.
- Subject's right to withdraw consent at any time during the study, with or without a stated reason.
- The principal investigator's opinion that it is not in the subject's best interest to continue study participation.
- Sponsor's decision to terminate the study.

**4.5.2 Procedures for Subjects Who Discontinued**

Subjects who discontinue from treatment should undergo the Study Completion evaluations tabulated in Section 6.1 for the purpose of safety monitoring within 7 days after their last dose of study medication. Any subject that discontinues with ongoing AEs should be followed until resolution of their AE(s) or until the PI has determined that the AE(s) has stabilized.

**4.5.3 Documentation of Withdrawal of Subjects**

Document the reasons for early discontinuation of any subject from the study on the appropriate case report form (CRF). If the reason for early discontinuation is an AE or an abnormal laboratory value, record the specific event or test result on the AE CRF, and monitor the subject until the event is resolved or deemed stable by the investigator.

**4.6 STUDY DISCONTINUATION**

The sponsor has the right to terminate this study or remove a participating site at any time. Reasons for terminating the study or site may include, but are not limited to, the following:

- The incidence or severity of AEs in this or other studies indicates a potential health hazard to subjects.
- Subject enrollment is unsatisfactory.
- Data recording is inaccurate or incomplete.
- Investigator does not adhere to the protocol or applicable regulatory guidelines in conducting the study.
- A decision from the Institutional Review Board (IRB)/Independent Ethics Committee (IEC), or regulatory authority to terminate the study.

**5.0 TREATMENT OF SUBJECTS****5.1 TREATMENT REGIMENS**

The treatment regimens through study completion are shown in Table 5.1-1.

**Table 5.1-1. Dosing Regimen**

| Cohort No.    | Study Drug Dose Level and Frequency                                                                                    |
|---------------|------------------------------------------------------------------------------------------------------------------------|
| Part 1 |                                                                                                                        |
| 1             | 6 subjects to receive a single oral 100-mg dose of AL-335 in a fasted state with 2 subjects receiving matching placebo |
| 2             | 6 subjects to receive a single oral 200-mg dose of AL-335 in a fasted state with 2 subjects receiving matching placebo |
| 3             | 6 subjects to receive a single oral 400-mg dose of AL-335 in a fasted state with 2 subjects receiving matching placebo |

| Cohort No.    | Study Drug Dose Level and Frequency                                                                                                                                                                                                                                                                                                                                                                                                                                                                                                                                    |
|---------------|------------------------------------------------------------------------------------------------------------------------------------------------------------------------------------------------------------------------------------------------------------------------------------------------------------------------------------------------------------------------------------------------------------------------------------------------------------------------------------------------------------------------------------------------------------------------|
| 4             | 6 subjects to receive a single oral 800-mg dose of AL-335 in a fasted state with 2 subjects receiving matching placebo                                                                                                                                                                                                                                                                                                                                                                                                                                                 |
| 5             | 6 subjects to receive a single oral 1,200-mg dose of AL-335 in a fasted state with 2 subjects receiving matching placebo                                                                                                                                                                                                                                                                                                                                                                                                                                               |
| 6             | 6 subjects to receive single 400 mg oral dose of AL-335 (oral suspension formulation) in a fed state, with 2 subjects receiving matching placebo                                                                                                                                                                                                                                                                                                                                                                                                                       |
| 7, 8          | Two additional dose cohorts of AL-335 may be enrolled at the discretion of the Sponsor and the PI based on the emerging PK profile and the presence of an acceptable safety profile. Per cohort, six (6) subjects will receive single oral dose of AL-335 in a fed or fasted state at a dose to be determined and administered as either a tablet or oral suspension, with 2 subjects receiving matching placebo                                                                                                                                                       |
| Part 2 |                                                                                                                                                                                                                                                                                                                                                                                                                                                                                                                                                                        |
|               | 8 subjects who received the 3rd dose fasted in Part 1 (Cohort 3) will also receive AL-335 or placebo in fed (high fat meal) conditions after an 11-21-day washout period.                                                                                                                                                                                                                                                                                                                                                                                              |
| Part 3 |                                                                                                                                                                                                                                                                                                                                                                                                                                                                                                                                                                        |
| 1             | 8 CHC subjects (genotype 1) will be assigned to receive 400 mg of AL-335 given once daily on 7 consecutive days with 2 subjects receiving matching placebo in a fed state.                                                                                                                                                                                                                                                                                                                                                                                             |
| 2             | 8 CHC subjects (genotype 1) will be assigned to receive 600 mg of AL-335 given once daily on 7 consecutive days with 2 subjects receiving matching placebo in a fed state.                                                                                                                                                                                                                                                                                                                                                                                             |
| 3             | 8 CHC subjects (genotype 1) will be assigned to receive 800 mg of AL-335 given once daily on 7 consecutive days with 2 subjects receiving matching placebo in a fed state.                                                                                                                                                                                                                                                                                                                                                                                             |
| 4             | (Optional) 8 CHC subjects (genotype 1) will be assigned to receive AL-335 given once daily on 7 consecutive days in a fed state with 2 subjects receiving matching placebo. The dose to be administered will be determined by the Sponsor after completion of Cohort 3.                                                                                                                                                                                                                                                                                                |
| 5             | 8 CHC subjects (genotype 2) will be assigned to receive AL-335 given once daily on 7 consecutive days with 2 subjects receiving matching placebo in a fed state. The dose to be administered will be determined by the Sponsor after completion of the initial cohorts in subjects with genotype 1 CHC (no earlier than Cohort 2).                                                                                                                                                                                                                                     |
| 6             | 8 CHC subjects (genotype 3) will be assigned to receive AL-335 given once daily on 7 consecutive days with 2 subjects receiving matching placebo in a fed state. The dose to be administered will be determined by the Sponsor after completion of the initial cohorts in subjects with genotype 1 CHC (no earlier than Cohort 2).                                                                                                                                                                                                                                     |
| 7             | 8 CHC subjects (genotype 4-6) will be assigned to receive AL-335 given once daily on 7 consecutive days with 2 subjects receiving matching placebo in a fed state. The dose to be administered will be determined by the Sponsor after completion of the initial cohorts in subjects with genotype 1 CHC (no earlier than Cohort 2).                                                                                                                                                                                                                                   |
| 8             | 8 CHC subjects (genotype 1) with compensated cirrhosis (Child-Pugh A) will be assigned to receive AL-335 given once daily on 7 consecutive days with 2 subjects receiving matching placebo in a fed state. The dose to be administered will be determined by the Sponsor after completion of the initial cohorts in subjects with genotype 1 CHC (no earlier than Cohort 2). Sequence analysis of HCV NS5b from CHC GT1 cohorts assigned to receive either AL-335 or placebo will be completed prior to enrollment of subjects with compensated cirrhosis and CHC GT1. |

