##### 3.1.2 Secondary Objectives

To evaluate, after single and multiple doses of AL-335, the pharmacokinetics of AL-335, ALS-022399 and ALS-022227 (and other metabolites if applicable) in plasma and urine (single doses only)

To evaluate, after a single dose of AL-335, the effect of dosage formulation (tablet versus suspension) on the pharmacokinetics of AL-335, ALS-022399 and ALS-022227 (and other metabolites if applicable) in plasma

To evaluate the effect of food intake on the pharmacokinetics of AL-335, ALS-022399 and ALS-022227 (and other metabolites if applicable)

To evaluate the viral kinetics of HCV RNA in subjects with CHC infection treated with AL-335

To evaluate the viral resistance profile after 7 daily doses of AL-335 in subjects with CHC infection

To characterize the relationship between plasma exposures of AL-335 and/or its metabolites and viral kinetics

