### 3.2.2 Secondary Endpoints

- PK parameters of AL-335, ALS-022399, ALS-022227 (and other metabolites if applicable) following single dose administration:  $C_{max}$ ,  $t_{max}$ ,  $t_{1/2}$ , CL/F and  $V_z/F$  (for AL-335 only),  $AUC_{0-inf}$  or  $AUC_{last}$
- PK parameters of AL-335, ALS-022399, ALS-022227 (and other metabolites if applicable) following repeat dose administration:  $C_{max}$ ,  $t_{max}$ ,  $t_{1/2}$ ,  $AUC_{last}$  and  $AUC_{0-tau}$
- PK parameters of AL-335, ALS-022399, ALS-022227 (and other metabolites if applicable) following single dose administration in tablet form as compared with suspension:  $C_{max}$ ,  $t_{max}$ ,  $t_{1/2}$ , CL/F and  $V_z/F$  (for AL-335 only),  $AUC_{0-inf}$  or  $AUC_{last}$
- PK parameters of AL-335 (and metabolites if applicable) after a single oral dose in HV in fasted conditions as compared with fed conditions
- Concentration in urine and urinary excretion of AL-335, ALS-022399, ALS-022227 (and other metabolites if applicable) after a single oral dose in HV in fasted conditions
- HCV ribonucleic acid (RNA) viral load change from baseline in subjects with CHC infection
- Sequence analysis of the HCV NS5B region in subjects with CHC infection, as appropriate

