### 6.2.1 Diet, Fluid, and Activity

While in the Phase 1 unit, subjects in Part 1–3 will receive standardized diets at scheduled times that do not conflict with study-related procedures. In Part 1, prior to each dose of study medication, subjects may fast from food for at least 8 hours overnight until 4 hours postdose (SAD Cohorts 1-5). For the Optional SAD Cohorts (6-8), prior to each dose of study medication subjects will receive a standard meal and 250 mL of water. In Part 2, subjects will receive a single dose in a fasted state (Cohort 3 from Part 1) followed by a single dose in a fed state after an 11- 21 day washout. Except as part of dose administration, water may be consumed freely except between 1 hour prior to dosing and 2 hours post-dosing. In Part 3, prior to each dose of study medication, subjects will receive a standard meal and 250 mL of water.

Subjects in Part 2, the food effect study phase, will be given a standardized high-fat content meal within 30 minutes of their second dose; the meal will be completed at least 10 minutes prior to dosing. The meal will consist of the following ([CDER Guidance, 2002](#)):

- Two eggs fried in butter
- Two strips of bacon
- Two slices of toast with butter
- Four ounces of hash brown potatoes (fried with butter)

- Eight ounces (240 mL) of whole milk

Subjects will refrain from any strenuous activities from 48 hours prior to check-in through study completion. Consumption of grapefruit or grapefruit products such as juice are prohibited during study participation. Other prohibited foods that either inhibit or induce the CYP450 enzyme class are included in [Appendix C](#).

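### No arm the protocol commits to gives healthy volunteers the 400 mg tablet with the same meal as the 400 mg suspension, so the tablet-versus-suspension comparison mixes formulation with meal

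*Protocol*

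**What the plan says.** Section 3.1.2 sets out to evaluate "the effect of dosage formulation (tablet versus suspension) on the pharmacokinetics of AL-335" and two metabolites after a single dose. Section 3.2.2 turns this into an endpoint, PK parameters "following single dose administration in tablet form as compared with suspension", covering Cmax, tmax, half-life and AUC, with CL/F and Vz/F for AL-335. Section 1.2 gives the purpose: to learn whether the tablet needs further work.

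The arms bearing on this at 400 mg are:

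- **Suspension.** Part 1 Cohort 6 in Table 5.1-1: "6 subjects to receive single 400 mg oral dose of AL-335 (oral suspension formulation) in a fed state". The meal is defined in Section 6.2.1 and in footnote 3 to Table 6.1-1: "For the Optional SAD Cohorts (6-8), prior to each dose of study medication subjects will receive a standard meal and 250 mL of water".
- **Reference, first occasion.** Part 1 Cohort 3: "6 subjects to receive a single oral 400-mg dose of AL-335 in a fasted state with 2 subjects receiving matching placebo".
- **Reference, second occasion.** Part 2, where the Cohort 3 subjects "will also receive AL-335 or placebo in fed (high fat meal) conditions after an 11-21-day washout period".

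Table 5.1-1 leaves Cohorts 7 and 8 discretionary, "in a fed or fasted state at a dose to be determined", as tablet or suspension.

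**The concern.** A formulation comparison needs the two products given under the same conditions, or a way to adjust for the difference. Here the suspension is taken with one kind of meal and the presumed tablet reference with no meal or with another kind. If the two products performed identically, a difference could still appear because of the meal. If they differed, the meal could mask it.

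The protocol's own preliminary data show that this is not purely theoretical. Section 1.1 reports that high-fat food delayed tmax for AL-335 and both metabolites and slightly raised AUC for AL-335 and ALS-022399. At stake is the reading of a secondary objective that feeds a decision about the tablet. The primary safety objective is not affected.

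**Working it through.** The protocol states no power, margin or sample-size figure for this comparison, so there is nothing to reproduce. The check is a cross-tabulation of the arms it commits to.

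**Step 1. Single-dose arms at 400 mg in healthy volunteers** (Table 5.1-1, footnotes to Tables 6.1-1 and 6.1-2, Section 6.2.1):

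| Meal | Tablet (implied) | Suspension |
|---|---|---|
| Fasted | Cohort 3, 6 active | none |
| Standard meal | none | Cohort 6, 6 active |
| High-fat meal | Part 2, same 6 active | none |

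No row has both formulations. Cohorts 1, 2, 4 and 5 are fasted and at other doses.

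**Step 2. Is there a match elsewhere?** Part 3 Cohort 1 gives 400 mg after a standard meal, but to patients with chronic hepatitis C on repeated dosing. Its Day 1 profile runs to 12 hours plus the Day 2 predose sample, against 168 hours in Part 1. Using it would exchange a meal difference for a population difference and a shorter single-dose profile.

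**Step 3. What the ratio estimates.** Write S for suspension with a standard meal, and T_fast, T_std and T_hf for the tablet in the three states (geometric means). The target is S / T_std. The available ratios are:

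- S / T_fast = (S / T_std) × (T_std / T_fast)
- S / T_hf = (S / T_std) × (T_std / T_hf)

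T_std is not observed in healthy volunteers, so the second factor in each line is unknown.

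**Step 4. Bracketing.** If the standard-meal tablet value lies between fasted and high-fat (an assumption), the two available ratios bracket the target. The bracket's width is the food ratio T_hf / T_fast, which Part 2 estimates within subjects. The protocol gives no value, so take 1.10, 1.25 and 1.50 as an assumed range. With identical formulations:

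| Assumed T_hf / T_fast | Apparent ratio v fasted | Apparent ratio v high-fat |
|---|---|---|
| 1.10 | 1.00 to 1.10 | 0.91 (1/1.10) to 1.00 |
| 1.25 | 1.00 to 1.25 | 0.80 (1/1.25) to 1.00 |
| 1.50 | 1.00 to 1.50 | 0.67 (1/1.50) to 1.00 |

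Section 1.1 calls the AUC increase slight, which points to the top of this table rather than the bottom. For tmax the same reasoning applies on the time scale, and the size of the delay is not given.

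**Step 5. Can this still be changed?** Section 1.1 counts 40 volunteers dosed by 10 April 2015, and 5 cohorts × 8 = 40 accounts for Cohorts 1 to 5. The protocol version is dated 15 April 2015. Cohort 6 therefore appears not to have been dosed when this version was issued. Adding Cohort 6 and one matched cohort gives 40 + 8 + 8 = 56, within the stated 64.

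**The case against.** The strongest reply is that the sponsor looked at food before fixing Cohort 6. Section 1.1 finds no significant Cmax change for AL-335 and ALS-022399 and no effect on Cmax or AUC of ALS-022227. It concludes that the food effect was not clinically relevant and that later cohorts could be dosed in either state. This stands, and it limits the likely bias for Cmax and for ALS-022227. It does not dispose of tmax, which is an endpoint of the formulation comparison. It is also a preliminary reading from 6 active subjects of high-fat against fasted; no standard-meal effect has been measured in healthy volunteers.

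A second reply is that a matched arm is already permitted. Section 2.1 lets the additional cohorts repeat a planned dose level as tablet or suspension. That is correct, so the gap is an uncommitted reference, not an impossible one. Still, a stated objective should not depend on an arm whose dose, meal and formulation are all open.

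A third is that the study is exploratory and PK detail is deferred to the SAP. That covers the reporting format, such as a ratio with its interval. An SAP can choose a comparator but cannot supply a meal condition that nobody received.

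Two stronger readings are tempting and are not supported. A reader might infer that the whole food effect enters the ratio as bias. That could apply at most against the fasted reference; against Part 2 only the standard-to-high-fat difference enters. A reader might also infer that analysis can do nothing about it. The two tablet states can bracket the answer if the standard meal lies between them. Nor does the low precision of 6 against 6 different subjects strengthen the point: it is a separate limitation, and meal matching would not change it.

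**Conclusion.** The point holds as a limited design weakness. Among the arms the protocol commits to, tablet and suspension share no meal condition at 400 mg in healthy volunteers, so the formulation comparison is mixed with meal. The consequence is probably modest for Cmax and for ALS-022227, real for tmax, and possible for AL-335 and ALS-022399 AUC. Its size cannot be stated, because the protocol gives no figures for the food effect.

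This rests on two readings. Cohort 3 and Part 2 are taken as tablet dosing because only Cohort 6 is labelled suspension and Section 1.2 presents the suspension as an added formulation; Table 5.1-1 does not say so. Cohort 6 is taken as not yet dosed from the count of 40. The matter is a cheap improvement to a secondary objective and gives no reason to doubt the study as a whole.

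A separate inconsistency also holds. The Synopsis study design and Section 2.1 put the additional cohorts under fed conditions, and Section 6.2.1 and Table 6.1-1 give Cohorts 6 to 8 a standard meal. The Synopsis dose regimen and Table 5.1-1 allow Cohorts 7 and 8 either state.

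**What to change.** Before Cohort 6 is dosed, make the meal condition of the suspension arm and its tablet reference the same. There are two routes, and the choice is the sponsor's:

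1. **Align Cohort 6 with a meal condition already used for the 400 mg tablet** (Cohort 3 or Part 2). No extra subjects are needed. The cost is that Cohort 6 no longer shares the Part 3 standard meal. Section 6.2.1 and footnote 3 of Table 6.1-1 must change, and if the fasted condition is chosen, so must the Synopsis, Section 2.1 and Table 5.1-1.
2. **Commit Cohort 7 or 8 to the tablet at Cohort 6's dose and meal.** This uses one optional slot of 8 volunteers within the stated 64 and keeps the Part 3 match.

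Under either route, identify the reference arm for the formulation endpoint in Section 3.2.2 and label the formulation of every cohort in Table 5.1-1. Changes need ethics and, as appropriate, regulatory approval under Section 11.0, so they are best made in one amendment.

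In the same amendment, reconcile the statements on the meal state of the additional cohorts across the Synopsis, Sections 2.1 and 6.2.1, and Tables 5.1-1 and 6.1-1. Settle also whether Cohort 6 is optional: Section 6.2.1 groups it with the optional cohorts, while Table 5.1-1 lists it without that label.
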